#### RQ4: exploratory analysis of well-being

4.2.5

To explore whether emotional well-being and stress change over the 14-day study period and whether these changes differ between the type and speak groups, a mixed-effects model will be used. Fixed effects will include group, day, and their interaction (Day × Group). Random intercepts and slopes for participants will account for within-subject variability and individual trajectories.

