## Research questions and hypotheses

2

Building upon the illustrated gaps in current research, this study investigates the potential of NLP applied to digital journaling data with the aim of monitoring and supporting students’ emotional well-being, while generating individualized feedback on the journaling content and evaluating the students’ preferences.

Primarily, we hypothesize that (RQ1) emotional well-being and stress levels can be predicted from journaling entries using NLP. Prediction accuracy is expected to be higher for spoken entries (transcribed speech) compared to typed entries. Secondly, we hypothesize that (RQ2) the participants will evaluate the individualized feedback positively, indicating its acceptability and potential to foster reflection and compliance. Thirdly, we expect (RQ3) higher *state self-control* and *trait self-control* to be associated with greater adherence to the study protocol, and will be negatively correlated with dropout rates.

Furthermore, we will undergo (RQ4) an exploratory analysis of the improvement of the students’ emotional well-being over the study period, including the difference when typing vs. speaking the journal entries. Lastly, (RQ5) the predictive performance of NLP models will be compared to that of human experts (psychotherapists and clinical psychologists) in an exploratory manner to gain a practical perspective on the models’ performance. If RQ1 and RQ2 should hold true, future work should proceed to explore the usage of NLP to provide feedback automatically.

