### Participants and recruitment

3.2

Eligible participants will be university students who (a) are at least 18 years of age, (b) possess an internet-enabled smartphone (iOS or Android), and (c) demonstrate adequate proficiency in German, defined as fluent comprehension and production in both spoken and written form. Exclusion criteria are intentionally kept to a minimum to promote broad accessibility. Participants will be excluded only if they are experiencing an acute mental health crisis that necessitates immediate clinical intervention (e.g., acute suicidality).

To minimize participant attrition, several incentive mechanisms will be implemented: (1) all participants will receive individualized feedback upon completion of the 14-day study period; (2) participants who successfully complete the study will be compensated with a €10 voucher redeemable at various online retailers; (3) three additional €50 vouchers will be allocated by lottery among participants within the upper 50% of compliance; and (4) psychology and cognitive science students at the University of Tuebingen will be eligible to obtain university-internal credits.

A non-probability convenience sampling strategy is applied. Recruitment will be carried out through several complementary channels. Primary outreach will occur via university-wide email distribution lists at the University of Tuebingen, where psychology and cognitive science students will be explicitly informed that participation qualifies for university-internal credits. Students from all other disciplines will likewise be eligible and encouraged to participate. Additional on-campus recruitment will be conducted through the display of posters in university buildings. Digital recruitment will include dissemination of study information via the official social media account of the University Hospital Tuebingen and the extension of outreach to students at other universities through targeted posts in messenger-based student groups.

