During recruitment, participants will be directed via QR code to the study homepage,^1^ where they can access detailed study information and complete the online registration. Figure 2 provides an overview of the registration process. Participants accessing the registration link will first be asked to confirm that they meet the eligibility criteria; individuals who do not meet these criteria will not be able to proceed. Eligible participants will then provide informed consent by affirming the relevant checkboxes. Using the contact information provided, the study team will send an email containing a personalized QR code directing participants to download a GDPR-compliant messenger service, which will be used to maintain contact with participants throughout the study and to manage data collection. The messenger service facilitates secure, direct communication between participants and the study team, allowing participants to submit individual inquiries via chat, which will be answered on a daily basis. The email will also include an instructional video guiding participants through the installation process and explaining the app’s functionalities. The personalized QR code grants each participant access to a unique user account linked to an individual identifier within the app. Once the application has been installed and activated, the participant will be formally enrolled in the study.

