### Sample size calculation

4.1

In this NLP study, classical power analysis is not directly applicable, as the model performance depends on several factors such as training data points, model architecture, and transfer learning effects. Therefore, based on preceding transfer learning literature, 500 data points (D) per group (type and speak) are targeted [60, 61]. Each participant is expected to contribute one data point daily over the study duration of 14 days (d). A dropout rate of 28% (r) is assumed based on comparable studies [62–64]. The number of participants is calculated to be 50 participants per group (100 total):$$N=\frac{D}{d\times (1-r)}=\frac{500}{14\times (1-0.28)}\approx 49.6\approx 50$$

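### The exploratory RQ4 model has no weekday term, so if start weekdays are unevenly spread, part of any weekend mood effect will appear as a 14-day change

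*Protocol article*

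**What the plan says.** Section 2 of the protocol article announces, as RQ4, "an exploratory analysis of the improvement" in students' emotional well-being, including the difference between typing and speaking. Section 4.2.5 states the purpose of the model: "To explore whether emotional well-being and stress change over the 14-day study period". It then gives the model. "Fixed effects will include group, day, and their interaction (Day × Group"), it states, and adds: "Random intercepts and slopes for participants will account for within-subject variability and individual trajectories". No weekday or weekend term is named there or elsewhere in the article. The word linear is not used, but a random slope for each participant implies that day is a numeric variable.

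On timing, Section 3.2 describes several recruitment channels. "Primary outreach will occur via university-wide email distribution lists at the University of Tuebingen"; posters, social media and messenger groups at other universities supplement this. Entry is individual: "Once the application has been installed and activated, the participant will be formally enrolled in the study". The article states no common start date and no start weekday.

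**The concern.** RQ4 asks two things: whether mood and stress change over the 14 days, and whether the change differs between groups. The second is a randomised contrast. The first is not, because both groups journal and there is no group without journaling. It rests on the overall day effect alone.

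It is easy to assume that 14 consecutive days balance the calendar. They balance the number of weekend days, but not their position. For someone who starts on Monday, weekends fall on days 6, 7, 13 and 14, which are late in each week and later than average in the series. If mood is better at weekends, that person's fitted trend rises with no true change. For a Saturday start it falls. Whether this reaches the pooled day effect depends on the mix of start weekdays, which the article does not give. At stake is the reading of a small pooled slope as improvement or deterioration, given that Section 2 already speaks of improvement.

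**Working it through.** **The plan's own figure.** The article gives no figure for RQ4. Its one sample-size calculation (Section 4.1) reproduces: 500 / (14 × 0.72) = 49.6, rounded to 50 per group. It targets data points for RQ1 and does not bear on this point.

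**Inputs from the article.** Days t = 1 to 14 (Section 4.1). Fixed effects group, day and Day × Group, with random intercepts and slopes (Section 4.2.5). MDBF scale 1 to 7 (Section 3.4.3). 28% dropout from 100 participants (Section 4.1), so 72 remain.

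**Assumptions not in the article.** A weekend effect of 0.2 to 0.5 points, equal on Saturday and Sunday. Complete 14-day records. No true trend. For the rejection rates, residual SD 1.0 and slope SD 0 or 0.05 per day.

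**Step 1: share of a weekend effect taken up by one participant's slope.** With w = 1 on Saturday and Sunday and 0 otherwise, the least-squares slope of w on day is Σ(t − 7.5)w / Σ(t − 7.5)², and the denominator is 227.5. Multiplying by 13 gives the day 1 to 14 change.

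| Start | Weekend days | Σ(t − 7.5)w | Share (× 13 / 227.5) |
|---|---|---|---|
| Mon | 6, 7, 13, 14 | 10 | +0.571 |
| Tue | 5, 6, 12, 13 | 6 | +0.343 |
| Wed | 4, 5, 11, 12 | 2 | +0.114 |
| Thu | 3, 4, 10, 11 | −2 | −0.114 |
| Fri | 2, 3, 9, 10 | −6 | −0.343 |
| Sat | 1, 2, 8, 9 | −10 | −0.571 |
| Sun | 1, 7, 8, 14 | 0 | 0 |

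**Step 2: average over start-weekday mixes.**

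- Even over seven days: the sums add to 0, so the share is 0.
- Even over Monday to Friday: (10 + 6 + 2 − 2 − 6) / 5 = 2, so the share is 2 × 13 / 227.5 = +0.114.
- Half on Monday, the rest even over the other six days: the other six shares average −0.571 / 6 = −0.095, so 0.5 × 0.571 − 0.5 × 0.095 = +0.238.
- All on Monday: +0.571.

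**Step 3: points on the 1 to 7 scale, and rejection rate of the day effect at nominal 5%.**

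| Start mix | Spurious change, weekend effect 0.2 to 0.5 | Rejection rate |
|---|---|---|
| Even, seven days | 0 | about 5% |
| Even, Mon to Fri | 0.02 to 0.06 | 5.4% to 8.6% |
| Half Monday | 0.05 to 0.12 | not computed for this mix |
| All Monday | 0.11 to 0.29 | 15% to 80% |

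The rejection rates come from a normal approximation to a test on participants' slopes. Simulation (8,000 runs per scenario) agreed in the scenarios checked.

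**Step 4: Day × Group.** In the same simulations (all-Monday, Monday to Friday and even starts) this test rejected in 4.7% to 5.0% of runs.

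**Step 5: individual slopes under even starts.** The mean of the squared shares is 0.131 and its root is 0.36. A 0.5-point weekend effect thus adds an SD of about 0.36 × 0.5 = 0.18 points to participants' least-squares day 1 to 14 changes, purely from the calendar.

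**Step 6: with a weekend indicator in the model.** The bias is 0 for every start weekday. The slope variance factor is 1 / (1 − r²), where r² = [Σ(t − 7.5)w]² / (227.5 × 2.857) and 2.857 = 4 − 16/14. For Monday or Saturday r² = 100 / 650 = 0.154, a factor of 1.18. For Tuesday or Friday it is 1.06, for Wednesday or Thursday 1.01, and for Sunday 1.00.

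**The case against.** The strongest reply is that the bias needs a condition the article does not state. Recruitment runs through several channels, and each person registers, receives a code by email and activates the app in their own time, which tends to spread starts. With an even spread the mean bias is exactly zero. With weekday-only starts it is at most about 0.06 points under these assumptions. This stands, and it limits the point. A reader might infer from the mass emailing that starts will cluster and that RQ4 will therefore report a false improvement. The documents do not support that: clustering is possible but nowhere described. The manual sending mentioned in Section 3.3 concerns daily reminders and says nothing about start dates.

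Second, RQ4 is labelled exploratory, and a pooled slope without a comparison group could not carry a strong claim of improvement in any case. That also stands. A reader might think the typing versus speaking comparison is compromised too; it is not, because randomisation protects it.

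Third, a condensed article may leave calendar covariates to a fuller plan, and a list of what a model will include need not be exhaustive. That is fair, and the article contains no false statement or contradiction here. It does, however, name its fixed effects, and the list as given leaves the overall trend exposed.

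A reader might also wish to carry the term into the RQ3 compliance model. The RQ3 hypotheses concern self-control rather than the day effect, and nothing calculated here supports that extension.

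**Conclusion.** The point holds conditionally and is minor. If day is a numeric trend and start weekdays are not evenly spread, the overall day effect in RQ4 absorbs between 0 and 57% of any weekend effect. The sign depends on the start weekdays: the mixes averaged above give shares from 0 to +0.57, while starts concentrated on Thursday to Saturday would make the share negative. In points, the range is 0 to 0.29 for an assumed weekend effect of 0.2 to 0.5; the upper end needs everyone to start on a Monday.

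Even starts remove the mean bias but not the calendar component of individual slopes, which ranges from −57% to +57% of a weekend effect. The article supplies neither the size of a weekend effect nor the start-weekday distribution, so the actual bias cannot be stated. The shares are exact for complete records only.

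**What to change.** Add a weekend indicator, or a seven-level weekday factor, as a fixed effect in the RQ4 model, derived from the entry date; Section 3.5 shows that entries carry date and time. Report the distribution of start weekdays alongside the result, so that readers can judge how much the calendar could matter.

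No extra data are needed. The weekend indicator removes the bias for any mix of start days, provided the weekend effect is similar on Saturday and Sunday; the weekday factor relaxes that condition. The cost is precision: slope variance may rise by a factor of up to 1.18 if all participants start on a Monday or Saturday, and by less otherwise. Removing weekday variation from the residual may offset some of this.

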#### Baseline survey

3.4.1

Prior to the start of the study, participants will complete several baseline questionnaires: a demographic questionnaire capturing medication use and health history (see Additional file 1 of the Supplementary Material to this article), an educational level questionnaire based on the International Standard Classification of Education—Fields of Education and Training 2013 [49], and the WHO-5 Well-Being Index (WHO-5) [50] assessing general well-being. In addition, mental health and stress will be evaluated using the 21-item Depression Anxiety Stress Scales (DASS-21) [51], while dispositional self-control will be measured with the Brief Self-Control Scale (SCS-K-D) [52]. All instruments were administered in their validated German versions.

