#### Baseline assessment

4.2.1

Baseline questionnaire data will be summarized descriptively, and Spearman’s rank correlations will examine relationships between DASS-21 subscales, WHO-5, and SCS-K-D scores. Differences by sex and randomized group (type vs. speak) will be explored using two-way ANOVA. *P*-values will be reported for reference, but the study is not powered to detect baseline differences.

Daily measures of mood (MDBF subscales), stress (PSS-4), and state self-control (SSCCS) will be analyzed using linear mixed-effects models with random intercepts for participants to account for repeated measurements. Baseline well-being measures (SCS-K-D, DASS-21, WHO-5) and group assignment will be included as fixed effects to explore whether baseline characteristics predict daily mood and self-control. Daily observations will be included only for days with completed journals; the models naturally handle these unbalanced repeated measures. Additionally, person-level averages of daily mood and state self-control may be correlated with baseline measures using Spearman’s rank correlation as a descriptive check.

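### The exploratory RQ4 model is valid but omits the WHO-5 and DASS-21 baselines already collected, so the group level difference is estimated less precisely than it could be

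*Protocol article*

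**What the plan says.** Section 2 describes RQ4 as "an exploratory analysis of the improvement of the students’ emotional well-being over the study period", including the difference between typing and speaking. Section 4.2.5 asks "whether these changes differ between the type and speak groups" and fits a mixed model: "Fixed effects will include group, day, and their interaction (Day × Group"). On the random part it says: "Random intercepts and slopes for participants will account for within-subject variability and individual trajectories". No baseline score appears.

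Section 3.4.1 lists "the WHO-5 Well-Being Index (WHO-5) [50] assessing general well-being" and states that "mental health and stress will be evaluated using the 21-item Depression Anxiety Stress Scales (DASS-21"). Section 3.3 places this survey before randomisation. Sections 3.3 and 3.4.3 place MDBF and PSS-4 only in the daily survey, completed after each entry.

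Section 4.2.1 models the same daily mood and stress scores with participant random intercepts: "Baseline well-being measures (SCS-K-D, DASS-21, WHO-5) and group assignment will be included as fixed effects". It lists no day term. Its stated aim is to see whether baseline characteristics predict the daily scores.

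**The concern.** No MDBF or PSS-4 value precedes the first typed or spoken entry, so day 1 is already a post-randomisation measurement. If modality shifts reported mood or stress at once and the gap then stays constant, Day × Group is zero and the effect sits wholly in the group level term. The discussion in Section 5 itself expects that journaling may act as an intervention.

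WHO-5 and DASS-21 are the only pre-randomisation measures of well-being and stress available to sharpen that level comparison. Leaving them out keeps all between-person variance in its standard error. The article would also produce two group coefficients for the same outcomes, one adjusted (4.2.1) and one unadjusted (4.2.5), without saying which one informs typing versus speaking.

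**Working it through.** **The plan's own figure.** Section 4.1 states that "500 data points (D) per group (type and speak) are targeted". With 14 days and 28% dropout, 500 / (14 × 0.72) = 49.6, rounded up to 50 per group. The figure reproduces. It counts data points for the language models and sets no precision target for RQ4.

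**Inputs.** From the documents: N = 100 (50 per group), 14 days, 28% loss. Assumed, because the documents give none: total variance 1 at mid-study; between-person share (ICC) 0.3 or 0.5; SD of individual slopes (s) 0.02 or 0.04 per day; intercept-slope correlation −0.2; baselines explaining R² = 0.10, 0.25 or 0.50 of between-person intercept variance. Day is centred at mid-study.

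**Group level difference, complete data.** SE = √{(4/100) × [ICC(1 − R²) + (1 − ICC)/14]}.

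| ICC | R² = 0 | 0.10 | 0.25 | 0.50 |
|---|---|---|---|---|
| 0.3 | √(0.04 × 0.350) = 0.118 | √(0.04 × 0.320) = 0.113 | √(0.04 × 0.275) = 0.105 | √(0.04 × 0.200) = 0.089 |
| 0.5 | √(0.04 × 0.536) = 0.146 | √(0.04 × 0.486) = 0.139 | √(0.04 × 0.411) = 0.128 | √(0.04 × 0.286) = 0.107 |

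**Day × Group, complete data.** SE = √{(4/100) × [s² + (1 − ICC)/227.5]}, where 227.5 = 14 × (14² − 1)/12 is the sum of squared centred days. With ICC 0.5 and s = 0.04: √{0.04 × (0.0016 + 0.5/227.5)} = 0.0123. The intercept variance does not enter, so a baseline main effect changes nothing.

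**With missing days.** Generalised least squares for the model with random intercepts and slopes gave these changes in SE when a baseline main effect is added:

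| Data pattern | Level, R² 0.10 | Level, R² 0.25 | Level, R² 0.50 | Day × Group |
|---|---|---|---|---|
| Complete | −4.3% to −4.7% | −11.3% to −12.4% | −24.4% to −26.9% | 0.00% |
| 28% of days missing at random | −3.6% to −4.2% | −10.2% to −11.6% | −22.4% to −25.7% | −0.01% to −0.19% |
| Monotone dropout | −3.7% to −4.3% | −10.1% to −11.5% | −21.9% to −25.1% | −0.13% to −1.50% |

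Adding baseline × day as well, with 28% of days missing and the baseline explaining 10% or 25% of slope variance, lowered the Day × Group SE by 0.1% to 3.9%.

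**Cross-check.** In 40 simulated trials fitted by mixed model (ICC 0.5, R² 0.25, s = 0.04, 28% of days missing), the mean SE of the level term fell from 0.148 to 0.130 (about 12%). The mean SE of Day × Group went from 0.01383 to 0.01380.

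**Coding of day.** The level gains above are for mid-study. If day counts from the first entry, the group coefficient is the day 1 difference (t = −6.5). Its variance is (4/100) × [ICC(1 − R²) + (1 − ICC)/14 + 2t × cov + t²(s² + (1 − ICC)/227.5)], with cov = −0.2 × √{ICC(1 − R²)} × s. For ICC 0.5, s = 0.04, R² 0.25:
- Unadjusted: 0.5357 + 0.0735 + 0.1605 = 0.7697, SE 0.175.
- Adjusted: 0.4107 + 0.0637 + 0.1605 = 0.6349, SE 0.159.

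The gain is 9%, against 12% at mid-study.

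**The case against.** The strongest reply is that RQ4 asks about differences in change, which is Day × Group, and that contrast gains almost nothing. This stands. A reader might infer that RQ4's typing-versus-speaking comparison loses much precision, or convert the loss into participants. With ICC 0.45, 10 observed days and a baseline correlation of 0.5 to 0.7, the variance ratios are 0.505/0.3925 = 1.29 to 0.505/0.2845 = 1.78. Those figures describe the level difference only and rest on favourable correlations that the documents do not give. At a correlation of 0.3 the same formula gives 0.45 × 0.91 + 0.055 = 0.4645, an SE reduction of about 4%.

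Second, Section 4.2.1 already yields a baseline-adjusted group coefficient. This largely stands. The two models serve different purposes and do not contradict each other. But the 4.2.1 model lists no day term or random slopes and is not presented as a modality comparison.

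Third, a reader might infer bias from chance imbalance or from baseline-related dropout. Randomisation keeps the unadjusted estimate valid, and its standard error already reflects chance imbalance. Nothing in the documents ties dropout to WHO-5 or DASS-21; the predictor they hypothesise is self-control. In a simulation with an assumed baseline correlation of 0.6, dropout depending on baseline equally in both groups caused no material bias. Dependence in one group only shifted the level difference by about 0.04 to 0.06 SD. Any missing-data benefit is therefore small and secondary.

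Finally, this is a condensed article and a fuller covariate list may exist elsewhere. That is why the point is an improvement and not an error. Still, Sections 4.2.1 and 4.2.4 name their person-level covariates and 4.2.5 names none.

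**Conclusion.** The point holds as a low-severity efficiency and consistency improvement to an exploratory analysis that is valid as written. On the assumed range of R² from 0.10 to 0.50, and with 28% of days missing, the SE of the mid-study level difference would fall by about 4% to 26%. Day × Group would gain roughly 0% to 4%, the upper end only if baseline also predicts the trajectory. All sizes depend on assumed variance components and on a baseline-to-daily correlation that the documents do not state. The documents do not support a claim of bias, of an invalid model, or of a material loss on the contrast RQ4 names.

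**What to change.** In Section 4.2.5, add baseline WHO-5 as a fixed effect for the three MDBF outcomes and the baseline DASS-21 stress subscale for PSS-4, optionally each with a baseline × day term. State how day is coded, preferably centred at mid-study, so that the group term is the average level difference. Report that adjusted difference with its confidence interval beside Day × Group. Say in one sentence how it relates to the group coefficient from Section 4.2.1, for example by using the same baseline covariates in both models or by naming one as the modality estimate.

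The cost is a line or two of text and one model degree of freedom per outcome, or two with the interaction. No new data are needed.
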